### Sample size

The reported minimally clinical important difference (MCID) between groups for the RMDQ varies. A between group MCID of 2 or 3 points is commonly reported.^23 35 36^ However, it has been suggested that a difference of 1.5 may still be important, particularly in the context of low intensity interventions.^23^ Whether delivered as a stand-alone intervention or coupled with brief telephone support, SupportBack is a low intensity intervention with the potential to be rapidly scalable. Consequently, we considered a between group change of at least 1.5 to be a meaningful difference in this context. For our repeated measures primary outcome, a difference of 1.5 points on the RMDQ over the follow-up period of 12 months, assuming an SD of 5 in line with the feasibility study,^23^ gives an effect size of 0.30. Alpha will be set to 0.025 to allow both interventions to be independently compared with the usual care alone arm. Using four repeated measures (6 weeks, 3, 6 and 12 months), and assuming a correlation between repeated measures of 0.7% and 90% power, requires 215 participants per arm. Allowing for 20% lost to follow-up, this gives a total sample size of 806.

### Data collection and management

Data are primarily being collected online. The LifeGuide intervention and data system collects consent, baseline data including demographics and follow-up data across the four time points (6 weeks, 3, 6 and 12 months). When first sent a link to the system following screening, if patients do not log on within a week, they are emailed to check that they received the link and advised to look in their spam mail. If there is no response, one telephone call is attempted by the research team.

With regard to follow up protocol, where there is no response to the online follow-up questionnaire emails, two reminder emails and text messages will be sent. Following continued non-response, a paper questionnaire pack with a prepaid envelope will be sent 1 week after the last email/text reminder. If the paper questionnaires are not returned within 2 weeks of being sent, a blinded research assistant will call the participant to complete the primary outcome measure (RMDQ), quality of life questionnaire (EQ-5D-5L) and pain severity. If the participant is happy to continue, further measures from the questionnaire battery at the respective follow-up point will be collected in this manner. The full follow-up protocol with the telephone calls will be implemented at 6 weeks and 12 months follow-up points. These two follow-up points are considered most important, capturing initial and long-term response. Calling at all time points may lead to increased dropout at later time points. Follow-up at 3 and 6 months will include all the above steps except for the phone calls. All participants will receive a £5 voucher when asked to complete questionnaires at the more distant time points of 6 and 12 months. Examples of data collection forms can be provided by the trial team on request.

### Statistical methods

Quantitative analysis will begin following cleaning and inspection of the data. Descriptive analysis will be conducted to determine outliers and distributions of the data. Where necessary, if data are not normally distributed, transformations will be applied or another appropriate distribution used. The primary analysis for the RMDQ score will be performed using a multilevel mixed model framework with observations at 6 weeks, 3, 6 and 12 months (level 1) nested within participants (level 2). Results will be reported adjusting for baseline severity in function, stratification factors and any prespecified confounders. The model will use all the observed data and makes the assumption that missing RMDQ scores are missing at random given the observed data.

As there may not be a constant treatment effect over time, a treatment/time interaction will be modelled and included if significant (at the 5% level), with time treated as a random effect. An unstructured covariance matrix will be used.

Analysis of secondary outcomes will also be conducted using linear regression for continuous outcomes and logistic regression for dichotomous outcomes, again controlling for baseline symptom severity, stratification factors and any potential confounders. The structure and pattern of missing data will be examined, if appropriate, and a sensitivity analysis based on data imputed using a multiple imputation model presented. Data will be analysed on an intention-to-treat basis (they will be analysed as randomised). We will also undertake a complier-average causal effect analysis,^37^ which compares compliant participants in the intervention group, with those in the control group whose characteristics are similar enough to the intervention group compliers to suggest they too would have complied with the intervention, given the opportunity to do so. Compliance for these analyses in the intervention arm will be defined as completing at least session 1 of the internet intervention. Session 1 contains the central rationale for the intervention; that PA is primary in the management of LBP and provides instructions and advice on goal setting. The latter sessions follow a similar format to the first introductory module. With regard to the physiotherapist telephone support arm, we consider per protocol to be receiving at least two of the three planned phone calls. The telephone element is designed to be pragmatic with the necessary flexibility to fit patients’ requirements. However, receiving at least two of three calls indicates that support was delivered over time; an important aspect in the design and integration with the internet intervention.

It is not anticipated that there will be significant practice level (cluster) effects but this assumption will be tested by comparing a fixed effect model to a random effects model. If there are significant practice level effects then, the model will include a random effect for practice (random intercept) and participant (random intercept and slope on time) to allow for between participant and practice differences at baseline and between participant differences in the rate of change over time (if significant at the 5% level), and fixed effects for baseline covariates.

No interim analyses are planned. Full details of the analyses to be undertaken will be set out in the statistical analysis plan and approved by the trial steering committee (TSC). Our full statistical analysis plan will be published on the trial website in due course (https://www.southampton.ac.uk/medicine/academic_units/projects/supportback2.page).

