**Methods and analysis:**

A three-parallel arm, multicentre randomised controlled trial will compare three arms: (1) usual primary care for LBP; (2) usual primary care for LBP and an internet intervention; (3) usual primary care for LBP and an internet intervention with additional physiotherapist telephone support. Patients with current LBP and no indicators of serious spinal pathology are identified and invited via general practice list searches and mailouts or opportunistic recruitment following LBP consultations. Participants undergo a secondary screen for possible serious spinal pathology and are then asked to complete baseline measures online after which they are randomised to an intervention arm. Follow-ups occur at 6 weeks, 3, 6 and 12 months. The primary outcome is physical function (using the Roland and Morris Disability Questionnaire) over 12 months (repeated measures design). Secondary outcomes include pain intensity, troublesome days in pain over the last month, pain self-efficacy, catastrophising, kinesophobia, health-related quality of life and cost-related measures for a full health economic analysis. A full mixed-methods process evaluation will be conducted.

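### A 5% test on the trial data decides whether treatment-by-time enters the primary model, and the protocol does not name the primary contrast once it does

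*Protocol article*

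**What the plan says.** The Abstract (Methods and analysis) defines the outcome over the whole follow-up: "The primary outcome is physical function (using the Roland and Morris Disability Questionnaire) over 12 months (repeated measures design"). The Sample size section powers "a difference of 1.5 points on the RMDQ over the follow-up period of 12 months", and adds "Alpha will be set to 0.025 to allow both interventions to be independently compared with the usual care alone arm". That is one difference for each of two comparisons.

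The Statistical methods section describes a "multilevel mixed model framework with observations at 6 weeks, 3, 6 and 12 months (level 1) nested within participants (level 2"). Because the treatment effect may not be constant over time, it then states that "a treatment/time interaction will be modelled and included if significant (at the 5% level), with time treated as a random effect".

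The only other statement about how time enters comes later in the same section. If practice-level effects prove significant, the model will have a random effect for practice and for "participant (random intercept and slope on time").

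Full details are deferred to a statistical analysis plan, which is not shown.

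**The concern.** The form of the primary model is settled by a test on the trial's own outcome data. If the interaction is not significant, the model gives one treatment effect per intervention, and that is the quantity the trial was sized for. If it is significant, the model holds several treatment effects and the protocol does not say which one answers the primary question. Candidates are the average over the four visits, the effect at 6 weeks, the effect at 12 months, all four visit effects, or a slope.

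These candidates can disagree sharply when the effect wanes or builds, which the protocol itself allows for. At stake are whether the primary result is fixed before the data are seen, and whether the stated 90% power and alpha of 0.025 apply to what is reported.

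**Working it through.** **Inputs from the protocol (Sample size):** difference 1.5; SD 5; alpha 0.025 per comparison; four repeated measures; correlation 0.7 (printed as a percentage, but only 0.7 reproduces the stated figure); power 90%; 215 per arm; 20% loss; total 806. **Assumptions added here:** two-sided alpha (it reproduces the stated figure), equal correlation between all visits, the same effect pattern in both intervention arms, visits as categories, known variance.

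**1. Which contrast was powered?** For the average of m = 4 visits, the variance factor is [1 + 3 × 0.7]/4 = 0.775.

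n = 2 × (2.2414 + 1.2816)² × 25 × 0.775 / 1.5² = 213.7 per arm, against 215 stated. Then 215 × 3 / 0.8 = 806.25, against 806 stated. The sample size is therefore that of the time-averaged difference.

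**2. Power at 215 per arm, alpha 0.025**
- Average of four visits: SE = √(2 × 25 × 0.775/215) = 0.425; 1.5/0.425 = 3.53; power 90.2%.
- One visit with a 1.5-point effect: SE = √(2 × 25/215) = 0.482; 1.5/0.482 = 3.11; power 80.8%. For 90% power this contrast would need 276 per arm.

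**3. How often would the term be included?** With two intervention arms and three visit contrasts each, the joint test has 6 df and a 5% critical value of 12.59. With the same pattern in both arms, the non-centrality is

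λ = 215 × (2/3) × SS / [25 × (1 − 0.7)] = 19.11 × SS,

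where SS is the sum of squared deviations of the four visit effects from their mean. All the patterns below average 1.5 points.

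| Effect at 6 weeks / 3 / 6 / 12 months | SS | λ | Term included |
|---|---|---|---|
| 1.5 / 1.5 / 1.5 / 1.5 | 0 | 0 | 5% |
| 1.75 / 1.5 / 1.5 / 1.25 | 0.125 | 2.39 | 17% |
| 2 / 1.5 / 1.5 / 1 | 0.5 | 9.56 | 62% |
| 2 / 2 / 1 / 1 | 1.0 | 19.11 | 93% |
| 0.5 / 1.5 / 2 / 2 | 1.5 | 28.67 | 99% |

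**4. How much can the choice of contrast matter?** Take a deliberately strong waning pattern of 2.5/2/1/0.5, again averaging 1.5. The term is included in over 99.9% of trials. Power per comparison is 90% for the average, 99.8% at 6 weeks and about 11.5% at 12 months. For the mirror-image building pattern, the two visits swap.

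**5. Type I error under the global null** (simulation, 400,000 trials, familywise over both comparisons)
- Average always reported: 0.046.
- Average unless the interaction is significant, then the 12-month visit alone: 0.049.
- Average unless the interaction is significant, then any visit at an unadjusted 0.025: 0.058. Among the 5% of null trials in which the term enters, this is 0.29.

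**The case against.** The strongest reply is that the rule governs only whether a term enters the model. A reader might infer that the protocol abandons the 12-month average once the interaction is significant. It does not say so. The Abstract and the Sample size section still point to one difference over 12 months, and an average can be estimated from a model with the interaction. This stands: the primary contrast is left open, not replaced.

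A reader might also infer from the random slope that time is linear, so that the reported coefficient would be an effect extrapolated to time zero. The text does not support this. The slope is a participant-level random effect, in a sentence conditional on significant practice effects, and nothing says that a time-zero coefficient would be reported. Nor would such a coefficient always lose power. Under the same assumptions with linear time, it has 34% power for the building pattern 0.5/1.5/2/2, but 98% to 99% for the waning patterns 2/1.5/1.5/1 and 2/2/1/1.

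The error-rate harm is small, and its worst figure needs an unadjusted any-visit reading that the protocol nowhere states. Requiring time as categories is partly a modelling preference.

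Finally, the unseen analysis plan may name the contrast. That softens the point but does not remove it. The significance-based inclusion rule is positively stated in the protocol, and a plan that follows the protocol inherits it.

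**Conclusion.** The point holds as a badly fixed rule: a preliminary 5% test shapes the primary model, and the contrast that then counts as primary is not named. The stated sample size and its 90% power belong to the average over four visits; a 1.5-point effect at a single visit has 81%. Effects that average the planned 1.5 points but wane mildly to moderately bring the term in for 17%, 62% or 93% of trials, so the undefined branch is not remote. The main harm is a headline contrast that could be chosen after seeing the data. Type I inflation is secondary, at worst about 0.058 against 0.046.

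The inclusion rates rest on the assumed effect patterns, SD 5, equal correlations of 0.7, the same pattern in both arms and a 6-df test. The point does not rest on the protocol dropping the average or reporting a time-zero effect, since it says neither. Severity: should fix.

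**What to change.** - Remove the condition that the treatment-by-time term depends on its significance, and always fit the term.
- State that the primary result for each intervention versus usual care is the equally weighted average of the four visit differences, tested at 0.025 with a 97.5% confidence interval, whatever the interaction test shows.
- Make the visit-specific differences and the interaction test secondary.
- Clarify that the random effect of time refers to the participant-level random part, and that the visits also appear in the fixed part. A four-level factor is the simplest form.

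The sample size does not change: 215 per arm gives 90.2% power for this contrast, and the familywise error over the two comparisons is 0.046. The cost is wording in the protocol and analysis plan, plus about six interaction parameters (two arms × three visit contrasts) in a model with 3 × 215 = 645 participants.

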### Identification, recruitment and screening

Two recruiting centres, Southampton and Keele (each with a team of telephone support physiotherapists) are working with National Institute for Health Research Clinical Research Networks to facilitate the recruitment of general practices. Potentially eligible participants will be identified in one of two ways:

Patients who have consulted with LBP in the last 2 months will be identified by general practice staff from computerised records of consultations. Practices will be asked to repeat the searches approximately three times, or until the target number of patients per practice has been reached. Resulting lists of patients identified by the search will be screened by a practice GP who will rule out patients based on aspects of the eligibility criteria that can be determined from patient notes.During a patient consultation and on entering a relevant diagnostic or symptom Read code into the patient electronic medical record, GPs will be prompted about the trial and patient eligibility by an automated ‘pop-up’ screen activated by the Read code. GPs will then screen for eligibility (using the inclusion/exclusion criteria listed) and patients identified as suitable will have their medical record electronically tagged. A download of ‘tagged’ patients will occur regularly, anticipated to be every 2 weeks. This method will be used in practices where possible. Participating general practices not implementing the ‘pop up’ Read code method can identify potential patients during consultation. Having considered eligibility the GP or nurse practitioner will provide the patient with an invitation pack.

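### The stated clustering structure considers only practice and omits physiotherapist, which is nested in the telephone arm alone, so the standard error for telephone support versus usual care may be too small

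*Protocol article*

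**What the plan says.** The Statistical methods section of the protocol article sets out a two-level primary model, with follow-up observations nested in participants. It then takes up clustering and considers practice alone: "It is not anticipated that there will be significant practice level (cluster) effects but this assumption will be tested". If practice effects prove significant, the random effects are to be for practice and for participant. No other cluster is named.

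Under Randomisation, allocation and blinding, patients are randomised individually, stratified by recruiting centre and baseline RMDQ level. Practice is not a stratum, and Study setting gives 140 to 180 practices. Under Identification, recruitment and screening, the two recruiting centres are described as "each with a team of telephone support physiotherapists". Under Interventions, telephone support is given only in the third arm: at most one hour over up to three calls, guided by a standard checklist.

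The Sample size section says "Alpha will be set to 0.025 to allow both interventions to be independently compared with the usual care alone arm". It arrives at its number "assuming a correlation between repeated measures of 0.7% and 90% power, requires 215 participants per arm" and makes no mention of clustering of any kind.

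**The concern.** With individual randomisation, each practice can contribute participants to all three arms. A good or poor practice shifts the arms together, so practice effects largely drop out of the between-arm contrasts.

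Physiotherapists are different. They exist in one arm only, and about 269 of the 806 participants (806/3) are to be supported by the two teams. If some physiotherapists obtain better outcomes than others, participants who share one are correlated, and randomisation does not balance this because usual care has no counterpart. This is a partially nested design. Adjusting for recruiting centre, as a stratification factor, removes a difference between the two teams but not differences between physiotherapists within a team.

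A model without this level treats the telephone-arm participants as independent. Whenever the physiotherapist ICC is above zero, it gives too small a standard error and too narrow a confidence interval for telephone support versus usual care, and rejects a true null hypothesis more often than the 0.025 allotted to that comparison.

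**Working it through.** **Inputs from the Sample size section.** Difference 1.5 RMDQ points; SD 5; four follow-up measures; correlation between measures 0.7 (printed with a stray percent sign); alpha 0.025 per comparison, taken as two-sided; power 90%; 20% loss.

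**Reproducing the plan's figure.** The variance factor for the mean of four correlated measures is f = (1 + 3 × 0.7)/4 = 0.775. Then

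n = 2 × [5 × (2.2414 + 1.2816)/1.5]² × 0.775 = 275.80 × 0.775 = 213.7,

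which is 214 per arm against the stated 215. The total is 3 × 215/0.8 = 806.25, against 806. The stated figure is therefore reproduced with no design effect. The standard error of the difference is √(2 × 25 × 0.775/215) = 0.425.

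**Adding physiotherapist clustering to one arm.** Neither the number of physiotherapists, K, nor the ICC is in the article, so both are assumed. Further assumptions: 215 analysed per arm, equal caseloads, every telephone-arm participant clustered under one physiotherapist, equal total variance in both arms, ICC defined on the participant's mean over follow-up, and a normal approximation.

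- Caseload m = 215/K
- Telephone-arm design effect DE = 1 + (m − 1) × ICC; usual care has DE = 1
- Ratio of true to naive standard error R = √((1 + DE)/2)
- Actual type I error of the naive test = 2 × P(Z > 2.2414/R)

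Worked case, K = 10 and ICC = 0.05: m = 21.5; DE = 1 + 20.5 × 0.05 = 2.03; R = √(3.03/2) = 1.23; type I error = 2 × P(Z > 1.82) = 0.068.

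| K (assumed) | ICC (assumed) | DE | R | Type I error |
|---|---|---|---|---|
| 20 | 0.01 | 1.10 | 1.02 | 0.029 |
| 20 | 0.05 | 1.49 | 1.12 | 0.045 |
| 10 | 0.01 | 1.21 | 1.05 | 0.033 |
| 10 | 0.05 | 2.03 | 1.23 | 0.068 |
| 6 | 0.01 | 1.35 | 1.08 | 0.039 |
| 6 | 0.05 | 2.74 | 1.37 | 0.101 |

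At ICC = 0 nothing changes (R = 1, type I error 0.025). With few physiotherapists, proper small-sample degrees of freedom would widen the interval beyond what R shows.

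**The case against.** **The analysis plan may cover this.** The article defers full details to a statistical analysis plan that is not shown, and an arm-specific random effect is typical content for it. That plan may well add one. But the article is not silent on clustering: it specifies the levels of the model, chooses the cluster to consider and lists the random effects. Followed as written, it omits the cluster that does not cancel between arms.

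**The ICC may be very small.** The calls are short, follow a standard checklist after shared training, are checked for fidelity, and are meant to avoid individual assessment and treatment advice beyond the website's content. This stands, and it makes the lower end of the range plausible: with 20 physiotherapists and ICC 0.01 the standard error is off by about 2%. It does not justify assuming zero, because the calls also draw on each physiotherapist's clinical skills, may address individual concerns, and are described as pragmatic and flexible.

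**The calculation assumes complete nesting.** Some participants may never be reached and so belong to no cluster, and the article does not say that one physiotherapist makes all of a participant's calls. Both would change the figures, and unreached participants would reduce them. The table is illustrative.

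**A reader might infer that power falls below the stated 90%.** The article does not support that. The 215 per arm takes no credit for baseline RMDQ, whereas the stated model adjusts for it. Assume a baseline-to-follow-up correlation of 0.5, so the variance factor falls from 0.775 to 0.775 − 0.25 = 0.525, and apply the ICC to the adjusted outcome. With ICC 0.05, power is then about 95% with 20 physiotherapists, 89% with 10 and 82% with 6. Higher baseline correlations or lower ICCs raise these figures. Holding the physiotherapist variance fixed instead lowers them somewhat (84% with 10). Power may therefore be above or below 90%, depending on values the article does not give.

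**A reader might also infer that testing for practice effects is itself a fault.** Since those effects largely cancel, the rule does little harm, and preferring another is a matter of taste.

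**Conclusion.** The point holds conditionally. The stated model considers a cluster that is crossed with treatment and omits one that is nested in a single arm. If the physiotherapist ICC is above zero, the standard error for telephone support versus usual care is too small and the type I error exceeds 0.025. Under the listed assumptions (6 to 20 physiotherapists, ICC 0.01 to 0.05), the understatement is a factor of about 1.02 to 1.37 and the type I error about 0.029 to 0.10. The upper end needs few physiotherapists and a high ICC together; the nature of the calls points towards the lower end.

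The article does not establish that the error bars are too narrow, that the teams are small, or that the trial is underpowered. The internet-only versus usual care comparison is not affected. This is a cheap improvement to one of the two primary comparisons, not a flaw that undermines the design.

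**What to change.** Prespecify in the statistical analysis plan, at least as a sensitivity analysis for the telephone comparison, a partially nested model. It would be the primary model plus a physiotherapist random intercept that applies in the telephone arm only, with Satterthwaite or Kenward-Roger degrees of freedom. State how participants who received no call, or calls from more than one physiotherapist, are assigned to clusters. Record the physiotherapist for each telephone-arm participant; the call checklists returned to the coordinating centre are a natural source, though the article does not say that they identify the caller. Report the number of physiotherapists, their caseloads and the estimated ICC. Add a sentence to the sample size justification that it assumes no physiotherapist clustering.

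The cost is some wording, one extra model and one identifier. No change to recruitment, randomisation or delivery is needed. The downside is a slightly wider confidence interval for the telephone comparison and, if there are few physiotherapists, an imprecise estimate of the variance between them.
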